## Study outcomes

The main primary outcome in this study would be the evaluation of serum concentrations of high-sensitivity C-reactive protein (hs-CRP). We will also consider the assessment of other inflammatory factors, including tumor necrosis factor-α (TNF-α), interleukin 6 (IL-6), and anti-inflammatory factor interleukin-10 (IL-10) as well as the assessment of disease severity and disease-related disabilities lipid profile, anthropometric measures, dietary intake, and physical activity, which all would be considered as secondary outcomes.

### Blood sampling and biochemical measurements

To assess blood factors, 10 cc blood sampling will be taken from all patients after 12 h of overnight fasting. The Westergren method will be used to measure the erythrocyte sedimentation rate (ESR). Previous studies have shown that this index is highly correlated with the severity of RA disease. In order to measure inflammatory factors, after separating the serum from the blood sample, the serums will be stored in a − 80 °C freezer until the tests are performed. Serum levels of inflammatory factors including hs-CRP, TNF-α, IL-6, and anti-inflammatory factor IL-10 will be measured by enzyme-linked immunosorbent assay (ELISA) method using the commercial kits. Serum concentrations of these indicators were strongly correlated with disease severity among patients with RA.

### Assessment of disease severity

Disease severity will be assessed using a valid DAS-28 scale [20]. The scale, designed by Prevoo et al. in 1995, evaluates 28 joints and consists of 4 components: (1) counting the number of swollen joints, (2) counting the number of painful joints, (3) ESR or hs-CRP levels, and (4) Global Health Score (Global Health) determined by visual analog scale (VAS) [20]. The total scores of the whole scale will vary from 0 to 9.4, and based on that score, patients will be classified into four categories: (A) individuals with a score of more than 5.1 would be called as those with a high disease activity, (B) those with a score between 3.2 and 5.1 will be defined as individuals with moderate disease activity, (C) patients with a score between 3.2 and 2.6 will be defined as individuals with low disease activity, and finally, (D) those with a score of less than 2.6 will be considered in remission stage (recovery) [18, 19]. This tool has previously been used in Iranian patients with rheumatoid arthritis, and the results have been acceptable [21–24].

### Assessment of disease related-disabilities

To examine the disease-related disabilities, we will apply the Health Assessment Questionnaire-Disability Index (HAQ-DI). Health Assessment Questionnaire (HAQ) was designed in 1978 by James F. Fries et al. at Stanford University and included five subscales [25]. One of its subscales is HAQ-DI which has been used as an independent questionnaire in several studies [25]. This scale consists of 20 questions in 8 categories, and the range of scoring for each question varies from 0 to 3 (greater scores demonstrate more significant disability). To compute the overall HAQ-DI score, we used the average of eight categories’ scores. The total score of 0 to 1 will be considered mild to moderate disability, 1 to 2 as moderate to severe disability, and 2 to 3 as severe to very severe disability. We will not calculate the HAQ-DI score when a patient will not provide answers for more than two categories [25].

### Assessment of anthropometric measures

We will obtain data on anthropometric indices, including body weight, height, and BMI at the study baseline and end of the trial. Bodyweight will be measured in a fasting state, without shoes while wearing light clothing to the nearest 0.1 kg, using a weighing calibrated scale (Seca, Hamburg, Germany). Height will be measured by a mounted tape, without shoes and at a standing position to the nearest 0.1 cm using a stadiometer (Seca, Hamburg, Germany). BMI will be calculated by dividing weight in kilograms by height in meters squared.

### Assessment of dietary intake and physical activity

To ensure adherence to the intervention and avoid changes in dietary intakes throughout the study, assessment of dietary intake will be done using four dietary records throughout the study, one in every 3 weeks. Participants will be trained at the study baseline on how to record their dietary intakes. Days of dietary recording will be determined by investigators, such that two weekdays and two weekend days will be included in these recordings. Subjects will be requested not to change their usual dietary intakes on the day of recording their intakes. All records will be reviewed immediately, and possible problems will be resolved by interview. To compute nutrient intakes of study participants based on the analysis of these dietary records, we will use the Nutritionist IV software, in which the original database is based on the United States Department of Agriculture (USDA) food composition table; however, a modification will be done for the Iranian local foods.

To ensure a lack of difference in activity levels between intervention and non-intervention groups throughout the study, physical activity will be assessed by asking study participants to record their usual activities on specific days. The number of physical activity records will also be four, including two weekdays and two weekends. All the records will be taken once in 2 weeks. Therefore, all patients will complete four dietary records and four physical activity records during the study. Data from physical activity records will be processed using MET-h/day values given for each physical activity based on published guidelines [26].

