### Study design and intervention

The diagram for Standard Protocol Items: Recommendations for Interventional Trials (SPIRIT) is shown in Fig. 2. After recruiting participants, they will be stratified based on age (20 to < 40 and 40–60 years), BMI (< 30 and ≥ 30 kg/m^2^), and type of medicines (nonsteroidal anti-inflammatory drugs (NSAIDs)/disease-modifying antirheumatic drugs (DMARDs)/steroids/immunosuppressive) into different blocks and then will be randomly allocated to the intervention or control groups. For each patient in a particular block, a matched person in terms of the abovementioned variables would be placed in that block. Then, these two patients in a given block would be randomly assigned to the intervention and control groups. To do randomization, an identification code will be given to each eligible patient in each block, and then, the code of patients with the same age, BMI, and medication will be stated in the lottery container. A person who will be unaware of the study aims will be asked to draw the codes out of the container randomly. The first code will be assigned to the intervention group and the second code to the control group. This will be done for all containers. All patients, researchers, rheumatologists, statistical analysts, and laboratory staff will be blind to the intervention. Random allocation will be done by a third person who is unaware of the aim of our study. Patients in the intervention group (*n* = 20) will receive 30 g/day low-salt and low-fat probiotic cheese. Participants in the control group (*n* = 20) will receive low-salt and low-fat cheese without probiotics. Packaging of both kinds of cheeses would be in the same shape and color. The intervention will last for 12 weeks. Assessment of primary and secondary outcome variables will be done at the study baseline and end of the trial. A standard container will be given to participants, and they will be asked to that container to make sure they are consuming the specified amount. Participants will be asked not to change their lifestyle, dietary habits, and medicines throughout the study. To assess dietary intakes throughout the study, we will fill four 1-day 24-h dietary recalls (including two working days and two non-working days) once every 3 weeks by telephone interview. To complete dietary recalls, participants will be asked to report dietary intakes based on household measures. Then, we will convert the reported amounts to grams using available booklets. The average dietary intakes in these 3 days will be considered as participants’ mean dietary intakes throughout the intervention. To obtain nutrient intakes based on these food recalls, we will use the Nutritionist IV software (based on US National Nutrient Databank) modified for Iranian foods. In addition, four 1-day physical activity records (including two working days and two holidays) will be completed from all patients at weeks 3, 6, 9, and 12 of intervention to assess physical activity during the study. Participants will be requested to report all activities they have during a specific day with the name and type of activity as well as the time spent. All participants will be educated on how to record their activities throughout the study before the start of the trial. Furthermore, patients in both groups will be asked not to change their physical activity throughout the trial.

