### Statistical analysis

Statistical analyses of all data will be performed using the SPSS software version 21.0 (SPSS Inc., Chicago, IL, USA). To handle non-adherence, we will use the intention-to-treat approach for data analysis. Missing values will be dealt with using the last observation carried forward (LOCF) method. Data will be expressed as mean ± standard deviations (± SD) and percentages. The one-sample Kolmogorov–Smirnov test will be used for assessing the normality of the distribution of data. In the case of a non-normal distribution of a variable, we will apply the log transformation. If the variables were non-normally distributed even after log transformation, we would use non-parametric tests in the analyses. Continuous variables will be compared between the two groups by independent samples *t*-test (or its non-parametric equivalent). We will apply the chi-square test to examine the distribution of participants in terms of categorical variables. To find the effect of the intervention on outcome variables, repeated measures analysis of variance (or its non-parametric equivalent) will be used. In these analyses, the effect of the intervention, time, and time-intervention interaction will be explored. The potential difference in baseline levels of outcome variables as well as differences in dietary intakes and physical activity levels, if any, between the two groups will be controlled for in these analyses. *P* values will be considered significant if they were < 0.05.

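### Diet and physical activity are secondary outcomes promised at baseline and end, but the recording schedule cannot supply both, and these largely on-treatment measures are then used to adjust the outcome models

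*Protocol article*

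**What the plan says.** Four statements in the Protocol article bear on this point.

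- **Status.** Study outcomes ends its list with "dietary intake, and physical activity, which all would be considered as secondary outcomes".
- **Timing.** Study design and intervention states: "Assessment of primary and secondary outcome variables will be done at the study baseline and end of the trial". It also says: "The intervention will last for 12 weeks".
- **Schedule.** For diet, the same section says "we will fill four 1-day 24-h dietary recalls (including two working days and two non-working days) once every 3 weeks by telephone interview", and Assessment of dietary intake and physical activity says "assessment of dietary intake will be done using four dietary records throughout the study, one in every 3 weeks". The recalls are then reduced to one average per patient, taken to represent intake over the whole intervention. For activity, Study design and intervention names weeks 3, 6, 9 and 12 of the intervention, whereas the assessment section gives a two-week interval. Both sections count four records of each kind. The only baseline step described is training in how to keep the records.
- **Use.** Statistical analysis plans a repeated measures analysis of variance for the outcome variables, with intervention, time and their interaction. It adds that "differences in dietary intakes and physical activity levels, if any, between the two groups will be controlled for in these analyses".

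**The concern.** Two problems follow from reading these statements together.

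First, the timing statement and the schedules conflict. If there is no baseline value for diet or activity, there is no change from baseline to report, and a repeated measures analysis from baseline to end cannot be run for them. A shift in habits when the study cheese is introduced would also go unseen, although participants are asked not to change diet or activity.

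Second, these measures enter the models for the other outcomes, including hs-CRP, the primary outcome. A covariate measured after randomisation may be affected by treatment. If the probiotic cheese eases symptoms and patients then move more or eat differently, adjusting for that difference removes part of the treatment effect or introduces bias. The adjustment is applied when the arms are seen to differ, which is when a treatment effect on the covariate is one of the possible explanations. Without a pre-treatment value, such an effect cannot be told apart from chance imbalance.

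**Working it through.** The plan gives no figure to reproduce on this point. The check is whether any reading of the schedule yields both promised time points, and what can still be estimated.

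**Inputs.** Number of records k = 4 for each measure. Interval d = 3 weeks (diet in both sections; activity as implied by its named weeks) or d = 2 weeks (activity in the assessment section). Intervention length 12 weeks. All are from Study design and intervention and from Assessment of dietary intake and physical activity.

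**Step 1: span of the records.** Span = (k − 1) × d.
- d = 3: (4 − 1) × 3 = 9 weeks.
- d = 2: (4 − 1) × 2 = 6 weeks.

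Covering week 0 and week 12 needs a span of 12 weeks. Both spans fall short.

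**Step 2: all three-week schedules that fit into weeks 0 to 12.**

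| Weeks | Baseline? | End? |
|---|---|---|
| 0, 3, 6, 9 | yes | no |
| 1, 4, 7, 10 | no | no |
| 2, 5, 8, 11 | no | no |
| 3, 6, 9, 12 | no | yes |

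At two-week spacing, only 0, 2, 4, 6 includes baseline and only 6, 8, 10, 12 includes the end. No schedule includes both.

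**Step 3: which reading applies.** For activity, weeks 3, 6, 9 and 12 of the intervention are named, so there is an end value and no baseline. For diet no weeks are named. That the records are averaged as intake over the intervention, and that baseline is mentioned only for training, points to the same pattern.

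**Step 4: what remains estimable.** With records at weeks 3, 6, 9 and 12 in two arms, a group-by-time model has 1 intercept + 1 group + 3 time + 3 interaction = 8 parameters, and there are 2 × 4 = 8 cell means. The design matrix has rank 8 of 8. A within-treatment time-by-group effect is therefore estimable from the individual records, and so is a comparison of on-treatment means. For diet the time dimension is lost if only the planned average is kept. The text there reads "The average dietary intakes in these 3 days will be considered as", although four recalls are collected; that is a separate slip and does not alter this result.

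**Step 5: the adjustment.** Suppose treatment shifts the on-treatment covariate by δ, and the covariate shifts the outcome by β. In a linear model with no unmeasured common cause of the two, the unadjusted contrast estimates the total effect τ, and the adjusted contrast estimates τ − δβ. The document gives neither δ nor β, so the discrepancy δβ cannot be put in numbers. It is zero only if δ or β is zero. If covariate and outcome share an unmeasured cause, adjustment can bias the estimate further.

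**The case against.** The strongest reply is that these are mainly monitoring data. The assessment section gives their purpose as supporting adherence, avoiding dietary change, and confirming that activity does not differ between arms. The activity aim is a between-arm comparison during treatment, which on-treatment records answer directly with randomisation intact. Serial diet records can also show drift during the study. All of this stands, and it supports treating the two measures as process measures.

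A reader might infer that no time-by-group effect can be estimated for diet or activity at all. The document does not support that: Step 4 shows a within-treatment effect is estimable, and Statistical analysis does not define its interaction as a change from baseline. Only the baseline-to-end contrast is lost.

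A reader might also take it as stated that every diet record falls after randomisation. That is explicit only for activity. For diet it is a strong inference, and the SPIRIT chart that might show the timing is not reproduced in the text at hand. The inference does not carry the contradiction, however: if diet recording began at week 0, the week 12 value would be missing instead.

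Finally, adjustment for on-treatment covariates could be called a separate issue, since adding a baseline record would not by itself remove it. That is correct, and the fix therefore has to address the covariates directly as well as the timing.

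**Conclusion.** The concern holds in this form. For two listed secondary outcomes, the promise of baseline and end measurements cannot be met by four records at either stated interval, which span 9 or 6 weeks of the 12 required. Change from baseline and a baseline-to-end time-by-group effect are unavailable for diet and activity. On-treatment means can be compared between arms, as can within-treatment trends where the individual records are kept.

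The more consequential part is that outcome models, including the one for hs-CRP, are to be adjusted for between-arm differences in measures that are on treatment explicitly for activity and by strong inference for diet. That can bias the treatment effect. The size is unknown because the document gives no relevant figures. Collection of hs-CRP itself at baseline and end is unaffected, so the weight is moderate: the plan should be corrected, but the trial's main data are not compromised.

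This rests on there being four records in total, as both sections say, with no further baseline record beyond those described.

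**What to change.** **Preferred, wording only.** Reclassify diet and physical activity as on-treatment process measures reported by arm. Correct the baseline-and-end statement so that it no longer covers them. Remove them as covariates from the outcome models, and keep the planned adjustment for the baseline value of each outcome. This adds no procedure and costs almost nothing.

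**Alternative, if they are to stay secondary outcomes.** Take one of the four records before cheese is dispensed, re-space the others so that one falls at week 12, and adjust only for the pre-treatment value. Equal spacing would be 12 / 3 = 4 weeks, giving weeks 0, 4, 8 and 12. Moving one record to week 0 at the present three-week interval would not suffice, because the last record would then fall at week 9. The cost is one fewer on-treatment record (three instead of four) and a noisy baseline, since a single day is either a working or a non-working day.

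Under either option, the two activity intervals (the named weeks and the two-week interval) need to be reconciled, and the individual diet records should be kept if a within-treatment trend is to be examined.

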### Study sample size calculation

The required sample size was calculated based on the data from a previous study [27] considering a type I error of 5% (*α* = 0.05) and type II error of 20% (*β* = 0.20, power = 80%) and hs-CRP as the key variable. We considered the mean difference in serum hs-CRP levels of 5.71 between the two groups. Also, the average SDs reported for hs-CRP in the control and intervention groups were considered as 5.93. We used the suggested formula for parallel clinical trials and reached the sample size of 17 patients in each group.
$$ n=\frac{2\times {\left({Z}_{1-\frac{\alpha }{2}}+{Z}_{1-\beta}\right)}^2\times \mathrm{SD}2}{\mathrm{d}{}^2} $$$$ n=2\times {\left(1.96+0.85\right)}^2{(5.93)}^2/{(5.71)}^2=17 $$

Based on this formula and given a 20% drop-out in each group, we will need a sample size of 20 persons for each group.

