## Methods/design

### Participants

This study is a parallel superiority randomized clinical trial, with a 1:1 allocation ratio which will be done in 2021, in which participants will be recruited from Shariati Hospital, Tehran, Iran. Women who will meet the criteria will be included in the current study: (1) those aged 20–60 years, (2) have a body mass index (BMI) of 25–40 kg/m^2^, and (3) those who have been diagnosed with a mild to moderate RA. RA will be diagnosed by a rheumatologist using the American College of Rheumatology (ACR) criteria. Disease Activity Score-28 (DAS-28) > 3.2 will be considered as mild to moderate RA [18, 19]. Patients whose conventional medications (methotrexate, prednisolone, hydroxychloroquine, sulfasalazine) were not changed in terms of type or dosage over the past month will be included. Individuals with (1) other inflammatory diseases including pancreatitis and inflammatory bowel disease (IBD), (2) acute heart disease or kidney and liver disease, (3) gastrointestinal disorders or lactose intolerance, (4) those who are pregnant or lactating, and (5) those who were using antibiotics, pre-biotic or probiotic supplements, multi-vitamin, and mineral supplements during the last 3 months will not be included. The study would be restricted to non-smokers and non-alcoholic individuals. People who are routinely using probiotic-enriched foods in their usual diet will not be included as well. The exclusion criteria would be any alteration in the type or dosage of medicines during the intervention, taking dietary supplements or antibiotics, smoking and alcohol use throughout the study, and getting pregnant. We will also exclude patients who fasted the whole day during the study, as Muslims do during Ramadan. All participants will provide informed written consent. Moreover, the study protocol has been recorded on the IRCT website (IRCT20201120049449N1). The flow diagram of the project is shown in Fig. 1.

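### Read literally, the sample size squares the average of the two arms' SDs where the average variance belongs, so 17 per group is too small for 80% power if the SDs differ materially

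*Protocol article*

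**What the plan says.** The section on the sample size calculation takes hs-CRP, the primary outcome, as the key variable, "considering a type I error of 5"% and a "type II error of 20"%. The effect is set as follows: "We considered the mean difference in serum hs-CRP levels of 5.71 between the two groups". On the spread it says that "the average SDs reported for hs-CRP in the control and intervention groups were considered as 5.93". Neither arm's SD is given, and the text does not say whether the average is arithmetic or pooled. The figure 5.93 is squared in the standard two-mean formula with normal quantiles 1.96 and 0.85, and the authors "reached the sample size of 17 patients in each group". Then, "given a 20% drop-out in each group", the section concludes that "we will need a sample size of 20 persons for each group". The Participants section describes a parallel design "with a 1:1 allocation ratio". The Statistical analysis section names the independent samples t-test for comparing continuous variables between groups, and repeated measures analysis of variance for the intervention effect.

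**The concern.** In a comparison of two means with equal arms, the variance of the difference is (SD1² + SD2²)/n. The term 2 × SD² in the plan's formula stands for SD1² + SD2², so the single SD that belongs there is the root mean square, √((SD1² + SD2²)/2). An arithmetic mean of two SDs is never larger than this and equals it only when the SDs agree. Any error from this source therefore runs one way: variance too low, n too low, stated power too high.

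The plan gives some reason not to take equality for granted. The assumed gap between the arm means (5.71) is about as large as the SD itself (5.93), on a concentration that cannot be negative, and the Statistical analysis section foresees log transformation for variables that are not normal. That makes unequal SDs plausible but does not establish them. At stake is the 80% power claimed for the primary outcome, since the final 20 per group is built on 17.

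**Working it through.** **Inputs, all from the sample size section:** d = 5.71; SD = 5.93; two-sided α = 0.05 (z = 1.96); power 80% (the plan uses z = 0.85; the four-decimal value is 0.8416).

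**1. The plan's own figure.**
n = 2 × (1.96 + 0.85)² × 5.93² / 5.71² = 2 × 7.8961 × 35.1649 / 32.6041 = 17.03.
With 0.8416 in place of 0.85, n = 16.93. The stated 17 is reproduced. Power at n = 17 by the normal formula is 80.2%.

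**2. Unequal SDs, average held at 5.93.** The SDs are not in the document, so the ratio r (larger to smaller) is an assumption.
SD1 = 2 × 5.93/(1 + r), SD2 = r × SD1, effective SD = √((SD1² + SD2²)/2).
The variance is understated by the factor 1 + ((r − 1)/(r + 1))². For r = 2 this is 1 + (1/3)² = 1.111.

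| r | SD1, SD2 | Effective SD | Variance factor | n by normal formula (z = 0.8416) | Power at 17, normal |
|---|---|---|---|---|---|
| 1 | 5.93, 5.93 | 5.93 | 1.000 | 16.93 → 17 | 80.2% |
| 1.25 | 5.27, 6.59 | 5.97 | 1.012 | 17.14 → 18 | 79.7% |
| 1.5 | 4.74, 7.12 | 6.05 | 1.040 | 17.61 → 18 | 78.6% |
| 2 | 3.95, 7.91 | 6.25 | 1.111 | 18.81 → 19 | 75.9% |

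**3. Where the effect starts.** By the normal formula, 17 per group holds 80% as long as the effective SD is at most 5.942. With an average of 5.93, that allows SDs of about 5.55 and 6.31, a ratio of about 1.14. The required n stays within two patients of 17 up to a ratio of about 2.08.

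**4. t-test with equal SDs of 5.93.** This needs no assumption about the ratio. Noncentrality = 5.71/(5.93 × √(2/n)), with 2n − 2 degrees of freedom. At n = 17 the noncentrality is 2.81 with 32 degrees of freedom and the power is 77.7%. At n = 18 it is 80.1%.

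**5. The planned 20 per group, by t-test.** The plan's own 20% loss leaves 20 × 0.80 = 16.

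| r | All 20 analysed | 16 remain |
|---|---|---|
| 1 | 84.3% | 75.0% |
| 2 | 80.4% | 70.6% |

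**The case against.** The strongest reply is that no error has been shown. The text may use the word average loosely for a pooled SD. If so, 5.93 is the right input, the arithmetic is correct, and the main point falls away. This stands: without the two SDs, a reader cannot tell which case applies. One might infer that 17 per group is certainly wrong, or wrong whenever the SDs are not identical. The document supports neither reading, because the meaning of the average is open and a ratio up to about 1.14 does no harm by the plan's own formula. Nor does it give any basis for picking a large ratio and quoting the shortfall that follows.

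A second reply is that power at 17 is not the power of the trial. If all 20 per arm are analysed under the stated intention-to-treat approach, the t-test reaches 80% up to an SD ratio of about 2. Adjustment for baseline would help if baseline and final values correlate, and a log transformation would reduce level-dependent spread. This also stands in part, but each element is conditional. The Adverse events section removes participants who complain of certain harms or wish to quit. With outcomes measured only at baseline and end, a value carried forward for a participant lost before the end is the baseline value, which does not add the information of a completed patient. Baseline control is planned only if a difference appears. None of these features enters the stated calculation.

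A third reply is that the normal formula is common practice and costs only one patient per group against the t distribution. That is true, and it marks the t-test point as minor. It is still the one part that holds whatever the two SDs are.

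One could also argue that 17.03 should itself round up to 18. That rests on the rounded quantile 0.85; with 0.8416 the result is 16.93, so it carries no weight on its own.

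**Conclusion.** The point holds conditionally. Read as written, the calculation squares an average SD where the average variance is needed. That can only understate the variance, so 17 per group is too small and its 80% power too favourable if the SDs differ materially. The shortfall at 17 is under half a percentage point at a ratio of 1.25 and about 4 points at a ratio of 2. These ratios are assumptions, and the shortfall is nil if 5.93 is pooled or the SDs are close.

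Independently of the ratio, a t-test with SD 5.93 needs 18 per group rather than 17. The planned 20 per group covers that if all are analysed (84.3%), but not if the plan's own 20% loss occurs (75.0%). The second figure also reflects how the drop-out allowance was applied, which is a separate matter in the same section. A reader might infer that the trial as a whole is underpowered because of the averaging. The documents do not support that: with 20 analysed per group, 80% is kept up to a ratio of about 2.

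**What to change.** In the sample size section, state both SDs from the cited study and say how 5.93 was obtained. Replace it with √((SD1² + SD2²)/2), unless it is already that quantity. Recompute with the t distribution, and restate the power that 20 per group delivers, both with all 20 analysed and with the 16 left after the assumed drop-out. If 5.93 proves to be pooled, one sentence saying so settles the SD question, and only the t-distribution correction remains.

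The cost is one recalculation from a source that the sponsor has already used. No extra patients are asked for. The only downside is that the stated power may become somewhat less favourable.

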**Methods:**

This study is a randomized, double-blind clinical trial, in which forty patients with mild to moderate severity of RA will be randomly allocated to receive either 30 g/day probiotic cheese (*n* = 20) or only low-salt and low-fat cheese without any added probiotic (*n* = 20) for 12 weeks. Assessment of anthropometric measures and biochemical indicators, including serum concentrations of high-sensitivity C-reactive protein (hs-CRP), tumor necrosis factor-α (TNF-α), interleukin-6 (IL-6), and interleukin-10 (IL-10), will be done at the study baseline and end of the trial. In addition, disease severity and disability will be assessed by DAS-28 and the HAQ-DI questionnaire, respectively.

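### Twenty per group covers a 15% drop-out from the required 17, not the stated 20%; at 20%, 16 remain and power is about 78% by the plan's own formula

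*Protocol article*

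**What the plan says.** The section on sample size calculation in the protocol article takes hs-CRP as the key variable, with 5% type I error, 80% power and a formula that uses the two-sided critical value 1.96. Its planning values are: "We considered the mean difference in serum hs-CRP levels of 5.71 between the two groups"; and "the average SDs reported for hs-CRP in the control and intervention groups were considered as 5.93". From these the authors "reached the sample size of 17 patients in each group". The next step is the drop-out allowance: "Based on this formula and given a 20% drop-out in each group, we will need a sample size of 20 persons for each group".

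The enrolled number is consistent elsewhere. The abstract says that "forty patients with mild to moderate severity of RA will be randomly allocated", 20 to each arm; the section on study design and intervention repeats 20 per arm; and the design is "with a 1:1 allocation ratio". So 20 per group is the intended size, not a misprint in one place.

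Two other sections bear on what happens to patients who leave. The statistical analysis section plans intention-to-treat with last observation carried forward (LOCF). The adverse events section says that participants who want to quit will be excluded from the trial.

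**The concern.** A drop-out allowance exists so that, after the expected losses, the number left is at least the number the power calculation requires. Here it falls one short in each group. No stated input makes 17 required, 20% lost and 20 enrolled agree.

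hs-CRP is the primary outcome, and this calculation is the only justification given for the trial's size. If the trial ends with the drop-out its authors allowed for and finds no significant difference, readers will judge that result against 80% power for a difference of 5.71, which the plan's own formula does not give at 16 per group.

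**Working it through.** **Inputs (section on sample size calculation):** difference d = 5.71; SD = 5.93; two-sided alpha 0.05, z = 1.96; power 80%, for which the article prints z = 0.85 (more exactly 0.8416); drop-out 20%; enrolled 20 per group, allocated 1:1.

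**1. The plan's own figure.** n = 2 × (z₁ + z₂)² × SD² / d², with SD²/d² = 35.165/32.604 = 1.0785.
- With the printed 0.85: 2 × 2.81² × 1.0785 = 17.03.
- With 0.84: 2 × 2.80² × 1.0785 = 16.91.
- With 0.8416: 16.93.

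The 17 per group is reproduced.

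**2. The drop-out step.**
- Remaining after 20% loss: 20 × 0.80 = 16, below 17.
- Enrolment needed to keep 17: 17/(1 − 0.20) = 21.25, so 22 per group (44 in total).
- Drop-out that 20 per group can absorb: 1 − 17/20 = 15%.
- Multiplying instead of dividing gives 17 × 1.2 = 20.4, which becomes 20 only if rounded down. This may be how the figure arose, but the article does not say.

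**3. Power at what remains.** Normal approximation: power = Φ(d / (SD × √(2/n)) − 1.96).
- n = 16: 5.71/(5.93 × 0.3536) = 2.723; 2.723 − 1.96 = 0.763; Φ = 77.7%.
- n = 17: 5.71/(5.93 × 0.3430) = 2.807; 2.807 − 1.96 = 0.847; Φ = 80.2%.

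The same check by the two-sample t-test (non-central t, 2n − 2 degrees of freedom):

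| Remaining per group | Normal formula | t-test |
|---|---|---|
| 16 | 77.7% | 75.0% |
| 17 | 80.2% | 77.7% |
| 18 | 82.3% | 80.1% |
| 20 | 86.1% | 84.3% |

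On the t-test basis 80% needs 18 per group, so 20 enrolled absorbs 1 − 18/20 = 10%.

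**4. Difference detectable with 80% power**, by one method at a time.
- Normal: (1.96 + 0.8416) × 5.93 × √(2/n) = 5.87 at n = 16, against 5.70 at n = 17.
- t-test: 6.07 at n = 16, against 5.88 at n = 17.

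Losing the one patient per group raises it by 0.17 (normal) or 0.19 (t-test).

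**5. Does LOCF restore the power?** Outcomes are measured only at baseline and at the end of the trial, so carrying forward means carrying the baseline value. Assume that the 20% who leave contribute no between-group difference and that the SD stays at 5.93. All 20 per group are then analysed, but the expected difference falls to 0.80 × 5.71 = 4.57, and power is about 68% by the normal formula (66% by t-test). LOCF does not rescue the 80%.

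**The case against.** The strongest reply is that the slip hardly matters: one patient per group, 2.3 percentage points below 80% by the article's own formula, and none at all if drop-out is 15% or less. The drop-out rate is itself a planning guess, and correcting the sentence changes nothing in the population, endpoint, conduct or analysis. All of this stands and sets the severity. It does not make the printed sentence right.

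A second reply is that the planned analysis controls for baseline differences, which could raise power above that of a simple comparison of two means. That is possible. Suppose the baseline value explains a share r² of the variance, so that the SD becomes 5.93 × √(1 − r²). Power by t-test at 16 per group is then about 79% at r = 0.3, 82% at 0.4, 86% at 0.5 and 91% at 0.6. But these correlations are assumptions. The article gives none, its formula is unadjusted, and it plans the adjustment only if baseline levels differ. The stated 80% cannot rest on it.

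A reader might also go further than the document allows:
- **That 17 is itself wrong, because 17.03 rounds up to 18.** This is an artefact of printing 0.85; with 0.84 or 0.8416 the result is below 17.
- **That the normal formula is an error, because a t-test needs 18.** The article declares a standard approximation and applies it as declared. The t-test figure is a useful second reading, not evidence of a mistake.
- **That the detectable difference rises from 5.71 to 6.07.** This compares a normal-approximation input with a t-test result and roughly doubles the effect of the slip.

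**Conclusion.** The point holds as a mismatch between stated figures. Twenty per group covers a 15% loss from 17, not 20%. At the stated 20%, 16 per group remain, and power for 5.71 is 77.7% by the plan's formula or 75.0% by t-test. Neither LOCF nor the exclusion of those who quit restores 80%.

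The result rests on the article's own difference, SD, alpha and drop-out, and on an unadjusted comparison of two means. A reader might infer that the trial as a whole is underpowered or must enrol 44. The document does not support that: the shortfall appears only if drop-out exceeds 15% (10% on the t-test basis), and an adjusted analysis could have power above or below 80% depending on a correlation that is not given. Severity: should be fixed, and not critical.

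**What to change.** Keep 40 patients and replace the drop-out sentence, using one method throughout. Either of these would do:
- *Normal-approximation basis:* 20 per group allows for 15% drop-out (17 completers per group, 80% power); with 20% drop-out, 16 per group remain and power is about 78%.
- *t-test basis:* 20 per group allows for 10% drop-out (18 completers per group, 80% power); with 20% drop-out, 16 per group remain and power is about 75%.

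The two should not be mixed: claiming 80% power with 17 completers while noting that a t-test needs 18 would contradict itself. In the printed calculation, write 0.84 in place of 0.85, which gives 16.9 and so 17.

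If the authors prefer to state power for a baseline-adjusted analysis, they should give the assumed correlation and a range, such as the 0.3 to 0.6 shown above, and label it an assumption.

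The cost is one corrected sentence, one corrected constant and a slightly less favourable stated figure. No extra patients are needed and the conduct of the trial does not change.
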